## Abstract

**Background:**

Between 2 and 43% of patients who receive a new prescription in PC do not initiate their treatments. Non-initiation is associated with poorer clinical outcomes, more sick leave and higher costs to the healthcare system. Existing evidence suggests that shared decision-making positively impacts medication initiation. The IMA-cRCT assesses the effectiveness of the IMA intervention in improving adherence and clinical parameters compared to usual care in patients with a new treatment for cardiovascular disease and diabetes prescribed in PC, and its cost-effectiveness, through a cRCT and economic modelling.

**Methods:**

The IMA intervention is a shared decision-making intervention based on the Theoretical Model of Non-initiation. A cRCT will be conducted in 24 PC teams in Catalonia (Spain), randomly assigned to the intervention group (1:1), and community pharmacies in the catchment areas of the intervention PC teams. Healthcare professionals in the intervention group will apply the intervention to all patients who receive a new prescription for cardiovascular disease or diabetes treatment (no other prescription from the same pharmacological group in the previous 6 months). All the study variables will be collected from real-world databases for the 12 months before and after receiving a new prescription. Effectiveness analyses will assess impact on initiation, secondary adherence, cardiovascular risk, clinical parameters and cardiovascular events. Cost-effectiveness analyses will be conducted as part of the cRCT from a healthcare and societal perspective in terms of extra cost per cardiovascular risk reduction and improved adherence; all analyses will be clustered. Economic models will be built to assess the long-term cost-effectiveness of the IMA intervention, in terms of extra cost for gains in QALY and life expectancy, using clinical trial data and data from previous studies.

**Discussion:**

The IMA-cRCT represents an innovative approach to the design and evaluation of behavioural interventions that use the principles of complex interventions, pragmatic trials and implementation research. This study will provide evidence on the IMA intervention and on a new methodology for developing and evaluating complex interventions. The results of the study will be disseminated among stakeholders to facilitate its transferability to clinical practice.

**Trial registration:**

ClinicalTrials.gov, NCT05026775. Registered 30^th^ August 2021.

**Supplementary Information:**

The online version contains supplementary material available at 10.1186/s12875-022-01727-6.

## Background

### Prevalence and impact of non-initiation

Medication adherence is a broadly studied health problem with a high impact on clinical outcomes and mortality [1–3]. Studies have mainly focused on persistence-related problems, such as early discontinuation, and implementation-related problems, like suboptimal dosing [4, 5]. Recently, a growing interest in adherence problems at the moment of initiating a medication has arisen [6–8]. Initiation is defined as the moment “when the patient takes the first dose of a prescribed medication” [4]; therefore, adherence problems related to initiation occur in cases of “late or non-initiation of the prescribed treatment” [4].

Recent studies indicate that up to 43% of new treatments are not initiated [7, 8] and that the prevalence of non-initiation is between 6 and 28% in Primary Care (PC) in the European context [9–11]. Non-initiation is associated with higher costs to the healthcare system, mostly generated by productivity losses and an increased number of home visits (which suggest worse disease progress) [12, 13], representing an economic burden for healthcare systems in the short term [12–14].

### Cardiovascular Disease and Diabetes

Cardiovascular disease (CVD) and diabetes are highly prevalent diseases with high morbimortality, they are the leading causes of death worldwide [15], and have a significant social and economic impact [16, 17].

Between 2 and 43% of treatments for CVD and diabetes are still not initiated [7, 11]. Early discontinuation and poor treatment implementation are also highly prevalent. For example, early discontinuation rates range between 11% (statins) and 18% (ECA inhibitors) [18], and more than 30% of patients who initiated treatment for CVD and/or diabetes abandon it within the first 3 years [19].

Studies on non-adherence to CVD and diabetes treatments found that it worsens the control of the disease [20–23] thus increasing morbidity, mortality [19, 24, 25] and healthcare costs [14]. Even though these studies have focused on persistence and implementation, it is expected that non-initiation may add to these negative effects [6].

### Effectiveness of strategies aimed to improve initiation

Different approaches have been used to address adherence [26, 27] and the evidence suggests that multi-component and theory-based interventions have the best chance of improving adherence [28, 29].

Systematic reviews identified a series of factors related to the disease, treatment, patient and the healthcare system that affect the probability of initiation, including the absence of social support, the cost of treatment, patients’ age and country of origin and beliefs about medication [7, 8, 30]. However, results from quantitative studies do not completely explain this phenomenon.

A few studies have explored the motivations for non-initiation to medications using qualitative methods [31–35]. The Theoretical Model of Medication Non-initiation [34, 35] shows that users make a risk–benefit assessment of new prescriptions which is influenced by their beliefs regarding the disease and the medication, their feelings, health literacy and other cultural factors, as well as the relationship between the patient and the Health System (especially the general practitioner [GP] and the pharmacist) and their context [34, 35]. Fear of adverse effects, doubts about the effectiveness of the medication, pill burden, preference for lifestyle interventions and cost of treatment also affect initiation [31–35].

Previously, not much effort had been made to address non-initiation. Only 9 randomised controlled trials (RCTs) have been conducted to assess the impact of interventions on non-initiation; none evaluated a theory-based intervention and they were conducted in the United States [36–44]. Three studies were conducted in secondary care [36–38]; those combined technical and educational interventions but did not have a positive impact on initiation. Among the six studies that were conducted in the PC context of the United States, some consisted of reminders for patients, which increased treatment purchases [39–42, 44]. However, adherence is heavily affected by desirability bias and false negatives are common when patients feel observed [45–47]. Consequently, it is likely that patients only purchased medication when they were aware that health professionals knew that they had not filled their prescriptions. The last study was also based on reminders and aimed to identify and resolve barriers to adherence but neither had an impact on non-initiation [43].

### The Initial Medication Adherence (IMA) study

The IMA study has an effectiveness-implementation hybrid design [48]; it consists of a pragmatic cluster randomised controlled trial (cRCT) along with a process evaluation to understand the effect of the IMA intervention in terms of effectiveness and cost-effectiveness, and to redefine the intervention before its implementation. Hybrid designs aim to evaluate the effectiveness of interventions while gathering information for their implementation in clinical care [49, 50] and are expected to speed the translation of research findings into routine practice [49, 50].

The IMA intervention was developed within the Medical Research Council (MRC) Framework for Complex Interventions [51, 52]. Further details on the design of the intervention and process evaluation are described elsewhere [53].

Following the MRC guidelines, several studies were carried out to identify the evidence base and develop the theory on which the IMA intervention is based. Using real-world data (RWD), the prevalence of non-initiation was estimated to be 17% in Catalan PC; for CVD and diabetes treatments specifically, it ranged between 5.7% (ACE inhibitors) and 9.1% (antiplatelet). Factors explaining non-initiation were also identified [9, 18, 30]. Additionally, to understand patients’ motivations for non-initiation, two qualitative studies based on Grounded Theory were conducted [34, 35]. The results of these studies were used to generate the Theoretical Model of Medication Non-Initiation [34, 35]. Finally, the evidence on interventions aiming to improve initiation was reviewed.

An initial version of the IMA intervention was drafted taking into account all the available evidence; it was based on the Theoretical Model of Medication Non-Initiation [34, 35]. It is a multidisciplinary intervention that promotes health literacy and shared-decision making (SDM) to improve medication initiation and secondary adherence and reduce cardiovascular risk (CVR).

To increase the acceptability and transferability of the intervention, discussion groups were then conducted with GPs, nurses, community pharmacists and other healthcare professionals, who made suggestions for optimisation, defined the limitations of the intervention and anticipated barriers to its implementation.

Before a definitive cRCT, a pilot study with an integrated process evaluation was conducted to assess the feasibility and acceptability of the IMA intervention and to test the clinical trial design [54], and the IMA intervention was optimised and refined accordingly to its results [53].

The aim of the present paper is to describe the study protocol for the cRCT of the IMA intervention.

## Methods/design

### Study aims

The aims of the Initial Medication Adherence–cluster-randomised controlled trial (IMA-cRCT) are, first, to assess the effectiveness of the IMA intervention compared to usual care in improving medication initiation, secondary adherence and clinical outcomes in patients who have been prescribed a new treatment for CVD or diabetes in PC using a cRCT; and second, to evaluate the cost-effectiveness of the IMA intervention, in comparison to usual care, in terms of extra cost per reduction of cardiovascular risk, gains in quality-adjusted life years (QALY) and life-years gained (LYG) using a cRCT and economic modelling.

### Design

The IMA-cRCT study consists of a 7-month pragmatic cRCT with a 12-month follow-up, with an integrated process evaluation to understand the trial results and refine the intervention accordingly (methods are detailed elsewhere [53]), and economic modelling to provide long-term evidence of the cost-effectiveness and cost-utility of the IMA intervention. Figure 1 shows the summary of the IMA-cRCT study.

**Fig. 1 Fig1:**
[figure not shown]
Summary of the IMA-cRCT Research Project and timeline

The intervention assignment is cluster-based considering PC teams and two parallel arms: usual care in the control group and the IMA intervention in the intervention group. Twenty-four PC teams will participate in the trial.

The Standard Protocol Items: Recommendations for Interventional Trials (SPIRIT) checklist for study protocols [55, 56] is provided in Additional file 1. Details about the pragmatic design of the IMA-cRCT are provided in the Pragmatic Explanatory Consortium Indicator Summary (PRECIS-2) [57] wheel scheme in Additional file 2.

### Setting

The study will be carried out in the Spanish PC setting. PC health centres and community pharmacies from urban and rural areas in Catalonia, a Spanish region of four provinces with a population of 7.6 million people [58], will be included in the study.

The Spanish National Health System offers universal coverage, is funded from taxes and health service provision is mostly within the public sector. Most competencies of this public system are transferred to the seventeen regions which manage and organise public healthcare services within their area [59]. In Catalonia, the Catalan Health Service (CatSalut) is responsible for managing and organising the services of the public healthcare system. CatSalut outsources the provision of services with not-for-profit private and public providers. Its main health service provider at the PC level is the Catalan Health Institute, a public provider, covering 80% of the population [60].

PC is the point of access to the public system, acting as a gatekeeper for secondary care. PC manages the highest volume of prescriptions, which are issued by GPs and dispensed by community pharmacists. Following Clinical Practice Guidelines, GPs carry out health promotion and prevention, early detection, treatment and monitoring of the most prevalent health problems. Nurses also perform health promotion and prevention actions; additionally, they provide direct patient care by assessing patients’ needs, planning and delivering adequate care and evaluating the results. In recent years, SDM is being promoted in the healthcare community, although this patient-centred approach is recommended but not yet standardised.

Medications under study can be exclusively obtained at pharmacies with a prescription but patients have freedom of choice on which community pharmacy to use to buy prescribed medicines. Although healthcare professionals are encouraged to work in an interdisciplinary way, due to the context of the Spanish National Health System, it is difficult for PC professionals to work in coordination with community pharmacists regarding the management of prescriptions or medication [61, 62]. In Spain, Community pharmacies are considered private health establishments of public interest [63]. Pharmacies can have more than one owner but at least one of the owners must be a pharmacist [64]; however, each pharmacist can only be the owner of one pharmacy. There is no limit on pharmacists or pharmacy technicians working in community pharmacies and although the former are responsible for dispensing medication, technicians can also dispense medication under the supervision of a pharmacist. For this reason, there must be at least one pharmacist working in the pharmacy at all times.

In 2019, the Council of Official Colleges of Pharmacists of Catalonia, in collaboration with CatSalut, developed an alert embedded in the e-prescription system to inform pharmacists when a patient is starting a new treatment. This is aimed to help pharmacists to provide adequate information while dispensing the new treatment [65]. This tool is available in all Catalan pharmacies for some medications, including platelet aggregation inhibitors excluding heparin, and insulins, regardless of the IMA intervention.

The Spanish National Health System provides free-of-charge services (outpatient and inpatient care) with some exceptions, such as outpatient pharmaceutical prescriptions, which are subjected to cost-sharing for patients. The contribution is based on annual household income and working status. For pensioners, the level of co-payment can be 10% or 60% with different monthly maximum ceilings; for active workers, the co-payment level can be 40%, 50% or 60%, but no ceilings apply to these groups. There are also groups of people exempt from payment. Finally, most treatments for chronic conditions are subject to a 10% co-payment capped at 4,26€ per prescription [66–68].

### Study population

#### PC teams, GPs, and nurses

##### Recruitment and selection

The recruitment process follows both top-down and bottom-up approaches to identify and recruit PC teams and healthcare professionals.

A PC team is a group of GPs, nurses and other healthcare professionals who offer comprehensive care to a specific population. PC teams can work in one or more PC centres and large PC centres can accommodate more than one PC team. PC teams from all over Catalonia managed by the Catalan Health Institute will be assessed for eligibility (*n* = 287). A list of PC teams and their characteristics will be provided by the System for the Development of Research in Primary Care (SIDIAP). Pairs of PC teams will be randomly selected based on their location (rural/urban) and stratified according to certain non-initiation [9] predictors: PC teams located in urban areas will be stratified according to the number of practitioners in the PC team, the size of the catchment area population for each PC team, the socioeconomic status of the population and the proportion of immigrants; and PC teams located in rural areas will be stratified according to the socioeconomic status of the population. An ordered list of replacement PC teams with the same characteristics will be randomly generated for each pair of PC teams.

To avoid contamination between PC teams and community pharmacies, a maximum of one PC team will be selected for each municipality (in municipalities ≤ 100,000 inhabitants) or single PC teams per neighbourhood (in municipalities > 100,000 inhabitants). In the case of PC teams from adjacent municipalities, there must be a minimum distance of 3 km between each team’s working place. If a PC team does not fulfil the inclusion criteria, the following PC team from the list of replacements will be considered for participation. The inclusion of PC teams from all provinces will be ensured.

Randomly selected PC teams will be informed about the study and invited to participate. First, the PC Territorial Managers and team managers from the selected PC teams will be invited to explain and present them the project and will be asked to encourage GPs and nurses from their teams to take part in the study. If the team manager accepts to participate, the study will then be presented to the GPs and nurses in each team.

##### Inclusion criteria

Participating PC teams have to fulfil the following inclusion criteria: a) the PC team manager must be willing to participate in the study, commit to guaranteeing compliance with the ethical standards in the PC centre (see Ethics approval and consent to participate) and sign an informed consent for participation; and b) at least five GPs in urban areas or two GPs in rural areas who fulfil the inclusion criteria must be willing to participate at the moment of PC team inclusion. There is no minimum number of nurses required to participate.

To join the study, GPs and nurses have to fulfil the following inclusion criteria: a) to provide signed informed consent for participation in the clinical trial and the process evaluation; b) to attend the IMA intervention training entirely and c) not to anticipate a termination or interruption of employment (planning to change their place of work or taking sick/maternity/paternity leave) during the study period.

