As part of the implementation strategy of the IMA intervention, there are three inputs which are essential to achieve the intervention outcomes. First, top-down and bottom-up recruitment approaches are taken to increase professional engagement. Second, after the randomisation of the PC teams, healthcare professionals from the intervention group receive training on the IMA intervention, lasting 6 h. The training covers several aspects of non-initiation and other topics such as communication skills, health literacy and SDM. And lastly, decision aids have been designed to support the IMA intervention. These include one leaflet for each of the five pharmacotherapeutic groups and an *ad-hoc* website (available at: www.iniciadores.es). The leaflets will homogenise the intervention and provide tools to transmit the concepts of risk and benefit of the disease, treatment and alternatives. The leaflets contain a link to the website with a quick response code and this is considered a reliable source of information on CVD and diabetes. A full description of the intervention and its implementation strategy are described elsewhere [53].

Healthcare professionals in the control group will not receive training on SDM nor access to the decision aids and will be asked to provide usual care.

All participating professionals will receive a reinforcement session on the registry of clinical outcomes in the e-health records system and IMA-cRCT ethical standards.

PC team pairs will be randomised to the intervention and control groups and training sessions will be scheduled. Upon completion of training, each pair of PC teams will start the 7-month intervention in March 2022. The study period will last 7 months to account for healthcare professionals’ summer holidays, which last up to a month. During this time, the intervention will be applied to each patient meeting inclusion criteria. Figure 2 shows the trial flow-chart based on CONSORT guidelines.

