### Statistical analysis

All analyses will be conducted following the intention to treat principle, including all patients treated by the GPs who fulfil inclusion criteria.

Poor registration of clinical outcomes and CVR data in electronic medical records may generate missing values. To deal with missing data, we will first explore the pattern of the missing data by using logistic regression models to test whether the observed variables predict the presence of missing data. If the existence of missing data is indeed explained by observed variables, a Missing at Random pattern will be assumed and multiple imputations with chained equations will be used to impute missing data. If possible, the imputation models will use any covariate that is predictive of missingness as well as all the variables that will be later used in the effectiveness and cost-effectiveness models [80]. The number of imputations will be determined by the fraction of missing information [81, 82]. The subsequent analyses will be conducted in each of the imputed datasets and the estimators will be pooled using Rubin’s rules [81].

A descriptive analysis, based on sociodemographic variables and health problems, will be performed to compare groups at baseline. Characteristics of participating healthcare professionals will also be compared between groups. Continuous variables will be presented with means and standard deviation; categorical variables will be presented with frequency and percentages. Differences between groups in these variables will be estimated using multilevel linear regression for continuous variables and multilevel logistic regression for categorical variables, considering the group as the independent variable in both cases.

The impact of the intervention will be assessed overall and for each pharmacotherapeutic subgroup, i.e., the 3rd level of the Anatomical Therapeutic Chemical (ATC) Classification System [83].

All models will be controlled for patient sociodemographic and clinical characteristics that have been described in the literature as predictors of non-initiation [9, 18] and which show statistically significant differences between intervention and control group at baseline; and will be performed using multilevel techniques. The basic unit of analysis will be either prescription or patient, based on the analysis. All analyses will be clustered at the level of PC team and GP.

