##### Sensitivity analysis

Per-protocol analyses will be performed including only patients who received a prescription by those GPs who attended both training sessions. Additionally, two complete case analyses will be performed: one considering only those patients attended by GPs who completed the 7-month study period, and another using only non-imputed data.

To assess uncertainty in the output of the models, a sensitivity analysis will be performed without controlling the models for baseline covariates to assess their effect on the results of the cRCT [84].

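### Full attendance at post-randomisation, intervention-only training is a GP inclusion criterion, and the ITT set is defined by those criteria; applied literally, this filters one arm only

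*Protocol article*

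**What the plan says.** Four statements in the protocol article bear on who enters the primary analysis.

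- *PC teams, GPs, and nurses – Inclusion criteria.* Three conditions apply to GPs and nurses who join. The second is "b) to attend the IMA intervention training entirely". It is not limited to one arm.
- *Intervention.* The training is placed after allocation and in one arm: "after the randomisation of the PC teams, healthcare professionals from the intervention group receive training on the IMA intervention, lasting 6 h". For controls: "Healthcare professionals in the control group will not receive training on SDM nor access to the decision aids". The only session described for both arms has other content, namely data recording and ethical standards: "All participating professionals will receive a reinforcement session on the registry of clinical outcomes in the e-health records system".
- *Statistical analysis.* "All analyses will be conducted following the intention to treat principle, including all patients treated by the GPs who fulfil inclusion criteria". No time point is given at which the criteria must be met.
- *Sensitivity analysis.* A per-protocol set is defined as "including only patients who received a prescription by those GPs who attended both training sessions".

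Patients enter only through a prescription from a participating GP (*Patients – Inclusion criteria*), so whether a GP counts decides whether that GP's patients count.

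**The concern.** An ITT set in a cluster trial should be settled by facts known before allocation. Here one of the facts that defines it, completed training, arises after allocation and can arise in one arm only. A GP in an intervention team who misses part of the six hours would fail an inclusion criterion, and that GP's patients would drop out of the primary analysis. A comparable GP in the paired control team would stay in. If GPs who do not complete training differ from those who do in how often their patients fill new prescriptions, the arms stop being comparable within teams, although randomisation of the teams was sound.

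The primary outcome (initiation) is at stake. So are the secondary outcomes and the economic evaluation, whose main analysis also follows intention to treat. The per-protocol analysis would offer little protection: if the ITT set in the intervention arm already holds only fully trained GPs, the two sets largely coincide there.

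Incomplete attendance is not far-fetched. *Strengths and limitations* names high workload and the pandemic as threats to participation and fidelity. The 10% loss allowance in *Sample size* is for incomplete records, not for untrained GPs.

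**Working it through.** **1. The text, read two ways.**

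| Statement | Criterion means completed training | Criterion means commitment to attend |
|---|---|---|
| GPs meeting the criteria are counted when the team is included, before randomisation | Cannot be satisfied: no training has taken place | Consistent |
| Control professionals get no such training | No control GP could join | Consistent, if the commitment is conditional on allocation |
| ITT set is restricted to GPs meeting the criteria | Filters the intervention arm after allocation | No post-allocation filter |
| Separate per-protocol set based on attendance | Largely redundant in the intervention arm | Meaningful in the intervention arm |
| Per-protocol rule for controls | Not stated | Not stated |

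The wording supports the left column: the criterion describes an act, whereas the next one, on not expecting to leave the post, describes an expectation. The structure supports the right column. Nothing in the article chooses between them, and an analyst could build either set.

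**2. The plan's own figure.** Inputs from *Sample size*: 10% non-initiation, a 3-point reduction (to 7%), 80% power, 5% significance (two-sided assumed), ICC 0.01, 30 prescriptions per GP, 10% losses.

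- Per arm, unpooled: (1.960 + 0.842)² × (0.10×0.90 + 0.07×0.93) / 0.03² = 1,352.6
- Design effect: 1 + 29 × 0.01 = 1.29
- Total: 1,352.6 × 1.29 × 2 / 0.9 = 3,877.5, which rounds up to the stated 3,878
- GPs: 3,878 / 30 = 129.3, consistent with the stated 130

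The arithmetic is sound. The problem lies in the definition of the analysis set.

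**3. Possible bias if the filter is applied.** The article gives neither a non-completion rate nor an outcome rate for non-completers, so both are assumed. Suppose there is no true effect and overall non-initiation is p = 10%. Let f be the share of intervention GPs removed (equal numbers of patients per GP) and q the non-initiation among their patients. The retained GPs then average (p − f·q)/(1 − f), and the spurious benefit is f(q − p)/(1 − f).

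| f | q | Retained GPs | Spurious benefit (points) | Share of 3-point target |
|---|---|---|---|---|
| 10% | 12% | 9.78% | 0.22 | 7% |
| 10% | 15% | 9.44% | 0.56 | 19% |
| 15% | 13% | 9.47% | 0.53 | 18% |
| 20% | 12% | 9.50% | 0.50 | 17% |
| 20% | 15% | 8.75% | 1.25 | 42% |

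The bias is zero if f = 0 or q = p, and it changes sign if q < p.

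**4. Cost of keeping every listed GP.** Assume that non-completers deliver no effect, so the difference becomes 3 × (1 − f) points. The effective number per arm is 65 × 30 × 0.9 / 1.29 = 1,360.5. Using the normal approximation with pooled variance under the null:

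| f | Rates compared | Power | Total prescriptions for 80% power |
|---|---|---|---|
| 0% | 10.0% vs 7.0% | 80% | 3,890 |
| 10% | 10.0% vs 7.3% | 71% | 4,878 |
| 20% | 10.0% vs 7.6% | 60% | 6,272 |

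The 3,890 differs slightly from 3,878 because the pooled formula is used here.

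**The case against.** The strongest defence is that the criterion was only ever a promise to attend. GPs meeting the criteria are counted at team inclusion, and a pair is not randomised until both teams agree, so nobody can have completed the training when counted. A per-protocol set based on attendance has work to do only if the ITT set contains GPs who did not attend fully. A further sensitivity analysis is limited to GPs who completed the seven months, which suggests that the main set was meant to keep those who stopped early. The literal reading would also leave no control arm, which cannot have been intended. The article adds that professionals are paid for training time and that training can move online, both of which favour attendance.

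Most of this stands as evidence of intent. It does not remove the problem, because the article never calls the criterion a commitment and sets no time point for meeting it.

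The defence does rule out three stronger inferences that a reader might draw. First, that randomisation is broken in the primary analysis: this follows only if the criterion is enforced, some GPs fail it, and those GPs' patients differ. Second, that the ITT and per-protocol sets are identical in the intervention arm: this too depends on enforcement. Third, that the per-protocol rule empties the control arm: the article does not define the two sessions, and it refers the full description of the intervention to another publication, so all one can say is that the rule has no stated meaning for controls.

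**Conclusion.** The concern holds as a conflict in the text with a conditional risk of bias. As written, the GP criterion, the timing of training and the ITT definition combine into a post-randomisation filter that can act only in the intervention arm. The counting of GPs at team inclusion and the separate per-protocol set point the other way. These sections must be reconciled before the analysis set is built.

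Neither the size nor the direction of any bias can be derived from the article. The range of about 0.2 to 1.25 points rests wholly on the assumed 10–20% non-completion and 12–15% non-initiation. To say that the retained GPs would be the more motivated or better communicators, and so that the bias would favour the intervention, is conjecture. The need to settle the definition does not depend on these values, because it decides who enters the primary analysis.

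**What to change.** 1. Reword the criterion as willingness to attend the training if the team is allocated to it.
2. Fix the list of GPs, by signed consent, before each pair is randomised.
3. Define the ITT set as all eligible patients of every listed GP in both arms, whatever the GP's attendance.
4. Use attendance only for the per-protocol set. Say which two sessions are meant, and state an entry rule that control GPs can meet, for example attendance at the session on data recording and ethics given to both arms.

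This is a change of wording. No new data collection is needed, since outcomes for these GPs' patients come from SIDIAP. The cost is dilution: if untrained GPs deliver no effect, power falls from 80% to about 71% at 10% non-completion and about 60% at 20% (both rates assumed). The protocol should acknowledge this. If non-completion at that level is expected, it should also be allowed for in the sample size.
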